## Abstract

**Background:**

Traumatic brain injury (TBI) is one of the most important causes of acquired structural epilepsy, post-traumatic epilepsy (PTE), however, efficient preventative measures and treatment are still not available to patients. Preclinical studies indicated biperiden, an anticholinergic drug, as a potential drug to modify the epileptogenic process. The main objective of this clinical trial is to evaluate the efficacy of biperiden as an antiepileptogenic agent in patients that suffered TBI.

**Methods:**

This prospective multicenter (n = 10) interventional study will include 312 adult patients admitted to emergency care units with a diagnosis of moderate or severe TBI. Following inclusion and exclusion criteria, patients will be randomized, using block randomization, to receive double-blind treatment with placebo or biperiden for 10 days. Follow-up will occur at specific time windows up to 2 years. Main outcomes are incidence of PTE after TBI and occurrence of severe adverse events. Other outcomes include exploratory investigation of factors that might have benefits for the treatment or might influence its results, such as genetic background, clinical progression, electroencephalographic abnormalities, health-related quality of life and neuropsychological status. Analyses will be conducted following the safety, intention-to-treat and efficacy concepts.

**Discussion:**

We hypothesize that biperiden treatment will be effective to prevent or mitigate the development of post-traumatic epilepsy in TBI patients. Other health measures from this population also may benefit from treatment with biperiden.

**Trial registration:**

ClinicalTrials.gov, NCT04945213. Registered on June 30, 2021.

## Introduction

Traumatic brain injury (TBI) is one of the main leading causes of death and lifelong disability in the world. One of the most important neurological consequences following TBI is the development of post traumatic epilepsy (PTE), which is responsible for approximately 5% of all focal epilepsy etiologies in the general population [1]. TBI patients present a higher risk to develop epilepsy than the general population, with 10–20% cumulative probability in 5 years [2–4]. The type and severity of injury correlates with the likelihood for a person to develop epilepsy, varying from 2.9% for moderate TBI to 17–27% for those who had severe TBI [2, 5–7]. Importantly, risk of epilepsy reaches 50% for patients with penetrating head injury [8]. Besides the high incidence, the causative links between TBI and epilepsy are still not completely understood, and there is currently no clinically available treatment or strategy that influences the likelihood of PTE development after brain injury [9].

Preclinical studies showed that anticholinergic drugs have the potential to modify neural plastic processes hampering epileptogenesis in animal models of epilepsy [10]. Among these drugs, biperiden, a cholinergic antagonist acting in the muscarinic receptor, administered soon after brain injury, delayed the latency and decreased the incidence and intensity of spontaneous seizures after brain injury [11]. These results were recently corroborated by other groups [12].

As a subsequent step, the use of biperiden in the acute phase after brain injury showed to be safe in a small phase II clinical study, which also served to test the feasibility of an interventional and prospective trial [10]. Here, the present Phase III study was designed to evaluate the safety and efficacy of biperiden in preventing the development of PTE in adult patients, who have suffered moderate or severe TBI, in a larger multicenter prospective study. Other clinically relevant neurological outcomes due biperiden treatment will also be investigated. The aim of this study is to evaluate the efficacy and safety of biperiden in preventing the development of epilepsy in patients that suffered TBI.

## Materials and methods

It is a multicentric phase 3 randomized, double-blind clinical trial coordinated by Sociedade Beneficente de Senhoras, Hospital Sirio-Libanês (Brazil), throught a partnership with the Brazilian Ministry of Health and funded by the Programa de Apoio ao Desenvolvimento Institucional do Sistema Único de Saúde (PROADI-SUS, Brazil). The study was prospectively registered in ClinicalTrials.gov (NCT04945213). This reporting followed the recommendations of the Standard Protocol Items: Recommendations for Interventional Trials (SPIRIT Statement) [13] and the Template for Intervention Description and Replication (TIDieR-placebo) checklist [14].

Fig 1 presents the study plan including the schedule of enrolment, intervention, and assessments. A complete SPIRIT checklist for clinical trial can be found on the S1 Checklist.

**Fig 1 pone.0273584.g001:**
[figure not shown]
Biperiden study plan including the schedule of enrolment, intervention, and assessments*. *Standard protocol items recommendations for Interventional Trials (SPIRIT) diagram [13]. CT computerized tomography; ECG electrocardiogram, βHCG human chorionic gonadotropin β; PTE post-traumatic epilepsy; SAS symptomatic acute seizures; EEG electroencephalography; mRS modified Rankin scale; EQ-5D-3L EuroQol three-level; EQ VAS EuroQol visual analogue scale; WAIS Wechsler Intelligence Scale; RAVLT Rey Auditory Verbal Learning Test; FDT Five Digit Test; polymorphic ε4 allele of the apolipoprotein E gene. Time deviations in days (d) allowed for follow up visits in months(m): a 1m ± 5d; b 3, 6, 9, 12, 18, 24m ± 15d.

### Ethical considerations

This study follows the principles of the Good Clinical Practice (GCP–ICH6 R2) in Randomized Controlled Trial (RCT). The whole protocol has been reviewed and approved by the Research Ethics Committee of Sociedade Beneficente de Senhoras, Hospital Sírio-Libanês (CAAE No. 39005920.8.1001.5461). Because the emergency nature of TBI, the Research Ethics Committee allowed to initiate the study protocol without informed consent of patients (or relatives), which must be provided until 48h.

An external Data Monitoring Committee (DMC) formed by three experienced clinic-researchers will provide independent assessment of the continuity of the study consiÞring the safety, validity, ethical and scientific merit of the trial.

### Participants

The study will enroll adults (18 to 75 years) of both sex who fulfill the following inclusion criteria: meet the moderate or severe TBI criteria according with the Glasgow Coma Scale (GCS) [15], in such a way that GCS is between 6 and 12 at the accident scene and/or between 3 (if sedated) and 12 at hospital admission; have computerized tomography (CT) scan with evidence of acute intraparenchymal hemorrhage and/or contusion; able to receive the first dose of treatment or placebo within 12 hours of brain injury, regardless of the accident cause. Participants, or their relatives in the event of patient´s unconsciousness, will have to provide written informed consent within 48 hours from the beginning of the protocol. Exclusion criteria are: current use of biperiden or antiseizure drugs; history of epilepsy, presence of other conditions that could increase risk factors for epilepsy development, such as perinatal injuries, meningitis, encephalitis, neoplasia, acute stroke, neurodegenerative diseases; any condition precluding the use of biperiden such as pregnancy, glaucoma, benign prostatic hyperplasia, atrioventricular block or cardiac arrhythmias; megacolon or mechanical obstruction of the gastrointestinal tract and inability to perform follow-up visits (e.g. homeless patients); refusal to participate in the study and current enrollment in other clinical trial. Alcohol intoxication or other psychotropic drug use at hospital admission will not lead to protocol exclusion.

We intend to recruit participants with acute TBI from at least ten hospitals located at different regions from Brazil (North, South, Southeast, Midwest and Northeast). After a first screening at the emergency care unit (ECU) for confirming eligibility criteria (which requires standard CT scan for acute TBI cases, electrocardiogram and pregnancy test for safety), those who fulfill all criteria will be included in the study. Because the emergency scenario and the injury severity, when the participant is not able to inform his medical history and is not accompanied by an appropriate informant, consent to participate and exclusion criteria might be confirmed within two days of protocol beginning. Participants will be prospectively monitored at their respective neurology/neurosurgery centers.

### Randomization and allocation concealment

Patients will be randomly assigned to receive placebo or biperiden using a random table generated by STATA® v17 software, in a 1:1 rate, in random permuted blocks and considering the recruiting centers as a criterion for stratification. The allocation concealment will be assured using the REDCap (Research Electronic Data Capture), a web-based software platform [16, 17].

### Blinding procedures

The intervention and the placebo will be identical in appearance (color, volume and packaging). Participants, staff and outcome assessor will be blinded to participant assignments.

### Interventions

Within 12 h after TBI, participants will receive intravenous (i.v.) infusions of 5 mg of biperiden (1 mL; Cinetol, Cristália, Brazil) diluted in 100 mL of 0.9% saline (treatment group) or 1 mL of sterile vehicle (sodium lactate, lactic acid, sodium hydroxide and water for injections) diluted in 100 mL of 0,9% saline (placebo group), every 6 hours for 10 days after TBI, until completing 40 total doses.

Patients will receive all standard of care treatment indicated for their clinical condition according to the hospital protocol and will not be deprived of any other required treatment, including all types of anti-seizure drugs, because of their participation in this study, regardless of the randomization group (placebo or biperiden) or the protocol period (intervention or follow up). Patients can be discontinued from the protocol if they remove the consent to participate; in any health conditions that health care providers, with sponsor agreement, believe that it is to the advantage of the patient not to comply with the procedures specified in this protocol; in case of screening error when including patients with history of epilepsy predicted in the study exclusion criteria (when this finding cannot occur at the time of recruitment).

During the hospitalization period, blood samples will be collected to analyze the genetic profile of patients regarding the presence of the polymorphic ε4 allele of the apolipoprotein E gene (APOEε4). Laboratory analyses will be performed by a central laboratory (DASA, São Paulo, Brazil), which is accredited by the College of American Pathologists (CAP, Northfield, IL, USA). Additional patients’ information, such as occurrence of adverse events, sociodemographic data, occurrence of symptomatic acute seizures, unprovoked epileptic seizures starting 7 days after TBI and clinical evolution will be collected during the hospitalization period. Suspected and diagnosed severe adverse events will be reviewed and adjudicated by the Ethics Committee and the external Data Monitoring Committee.

### Follow-up

At hospital discharge, patients and their relatives will be asked to keep a diary of epileptic seizures and record all ictal events with detailed descriptions. Prospectively, patients will be followed up for two years, on periodic visits at 1, 3, 6, 9, 12, 18 and 24 months after TBI with a neurologist or neurosurgeon, in neurology centers, to assess the development of epileptic seizures. Specifically, seizure diary, clinical and neurological evaluation, which include the Portuguese version of the modified Rankin Scale (mRS) for neurologic disability [18], will be assessed. In case of prolonged hospitalization, follow up visits will occur at the hospital, as possible. Due to the COVID-19 pandemic, we anticipate performing some of these evaluations through telephone calls. Despite the limited clinical assessment promoted by this resource (e.g. loss of physical evaluation), it allows investigation over seizure occurrence.

Patients will be further monitored with electroencephalogram (EEG) at the same time points defined for clinical evaluation. EEG recordings will be analyzed by experienced neurophysiologists. Other personal aspects that might benefit from the treatment or might influence its results will also be evaluated on specific timepoints, as shown on Fig 1, which include: social data and quality of life assessed using the Portuguese version of EuroQol three-level version (EQ-5D-3L) and EuroQol visual analogue scale (EQ VAS) at 3, 6, 12 and 24 months after TBI; standard neuropsychologic tests, including test batteries (Vocabulary, Block design, Digit Symbol-Coding, Symbol Search and Digit Span) of the Wechsler Intelligence Scale III (WAIS III); Rey–Osterrieth complex figure; Rey Auditory Verbal Learning Test (RAVLT) and Five Digit Test (FDT) which will be applied by psychologists at 6 months and then 24 months after TBI.

Data will be collected in an electronic case report form (eCRF) using free web-based software platform REDCap. Data entry will be monitored by an independent researcher according to a predefined monitoring plan. Patient confidentiality will be ensured by using identification numbers. All records will be kept on file at the trial sites or the coordinating data center for 5 years. The frozen trial database file will be kept on file for 5 years.

### Outcomes

The primary and secondary outcomes as well as planned analysis are listed in Table 1.

**Table 1 pone.0273584.t001:** Planned analysis for primary and secondary outcomes.

Description	Measurement	Timepoint (months)
**Primary Outcomes **		
PTE incidence	Number of participants with unprovoked seizures	24
Serious adverse events occurrence	Number of participants experiencing at least one serious adverse event	24
**Secondary Outcomes **		
PTE incidence	Number of participants with unprovoked seizures	1, 3, 6, 9, 12, 18, 24
mRS score	Number of participants categorized according to total score of the mRS scale	1, 3, 6, 9, 12, 18, 24
EEG pattern	Number of participants presenting epileptiform discharges and electrographic seizures	1, 3, 6, 9, 12, 18, 24
Neuropsychological Status	Number of participants categorized according to percentile ranks of neuropsychological tools	6, 24
Quality of life score	Number of participants categorized according to specific and total scores of quality of life scales	3, 6, 12, 24

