For secondary outcomes, it will be considered the frequency and type of clinical seizures at each specific timepoint during the two years follow up. Also, the number of participants presenting epileptiform discharges and electrographic seizures on the electroencephalogram recording will also be analyzed. For the neuropsychological status participants will be categorized according to the specific percentile rank defined for each cited standard test. Five health-related quality of life domains (mobility, usual care, usual activities, pain/discomfort, anxiety/depression) will be covered and compared between groups according to specific and total scores.

Other outcomes include the mortality incidence and occurrence of non-serious adverse events during the two year protocol.

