### Statistical analysis

The statistic plan followed the Guidelines for the Content of Statistical Analysis Plan in Clinical Trials [20].

Sample size calculation was performed based on previous studies [1, 2, 5–8, 10, 21] using the Pocock formula [22]. Assuming a difference in reduction of PTE of 15% between the placebo and biperiden groups at 24 months, type 1 error (alpha) of 0,05 and type 2 error (beta) of 0.10 and 20% dropout rate, 156 patients per group would be required to provide 90% power with 5% level of significance. According to epidemiological data provided by a pilot study [10], we estimated that the inclusion pace could be 3–5 patients/center/month leading to study completion within 42 months.

The hypothesis used in the analysis is that biperiden is superior to placebo. All patients who receive at least one dose of randomized study drug will be included into the safety analysis and all patients who receive at least one dose of a randomized study drug and who has an evaluable follow-up data will be included in intention-to-treat analysis. Missing data will be handled by chained-equation multiple imputation methods considering relevant baseline and outcome variables. A complete case analysis will be presented as a sensitivity analysis.

We plan to analyze the primary outcome using logistic regression, adjusting for age and sex at baseline. The result of this regression will be an odds ratio representing the relative effect of the intervention compared to the placebo. Secondary outcomes will be analyzed using appropriate generalized linear models, including logistic and linear models. Planned subgroups include type of epileptic seizures and the presence of the polymorphic ε4 allele of the apolipoprotein E gene (Table 1).

An interim analysis will be performed at 50% recruitment considering the primary outcomes. At the interim enrollment point, the DMC will consider as criteria for early interruption of the study p<0.001 for safety and p<0.0001 for efficacy analysis. The Pocock [22] stopping boundaries, will be used as a reference rather than as a rigid rule. In addition, the DMC will also consider the effect on other secondary outcomes, in the occurrence of unpredicted adverse events and external new evidence available during trial conduction.

A confidence level of 95% will be assumed for all analyses that will be conducted using Stata v17.

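### Neuropsychological scores are defined as counts in percentile-rank categories, and Table 1's similar wording for quality of life does not match the text; analyse the numeric scores as scores.

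*Protocol article*

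**What the plan says.** The Outcomes section introduces its table with "The primary and secondary outcomes as well as planned analysis are listed in Table 1". In the secondary rows of Table 1:

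- Neuropsychological status, at 6 and 24 months, is "Number of participants categorized according to percentile ranks of neuropsychological tools".
- Quality of life, at 3, 6, 12 and 24 months, is "Number of participants categorized according to specific and total scores of quality of life scales".

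The text after Table 1 agrees with the table on the first: "For the neuropsychological status participants will be categorized according to the specific percentile rank defined for each cited standard test". On the second it differs. The five health-related domains "will be covered and compared between groups according to specific and total scores", with no mention of categories.

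Statistical analysis gives one sentence on models: "Secondary outcomes will be analyzed using appropriate generalized linear models, including logistic and linear models". It does not say which outcome takes which model.

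The Follow-up section lists the instruments: five WAIS III subtests, the Rey–Osterrieth figure, the "Rey Auditory Verbal Learning Test (RAVLT) and Five Digit Test (FDT) which will be applied by psychologists at 6 months and then 24 months after" injury, the EQ-5D-3L and the "EuroQol visual analogue scale (EQ VAS) at 3, 6, 12 and 24 months after TBI".

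**The concern.** The neuropsychological tests and the EQ VAS yield numeric scores. Counting participants by percentile category treats everyone within a band as equal. The comparison then depends on where the cuts fall, and a real shift in the scores is harder to detect.

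The stated measure also sits badly with the stated models. Of the other secondary outcomes, seizures and EEG findings are binary and the mRS is ordinal. The neuropsychological and quality-of-life scores are therefore the natural candidates for a linear model, yet Table 1 describes both as numbers of participants.

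At stake is how well the trial can answer a question it raises in its Discussion, namely whether early treatment benefits neuropsychological function and quality of life. Psychologists apply a full battery at two visits, and banding would leave part of that information unused.

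**Working it through.** **Plan's own figure.** The article gives no power or sample-size figure for these scores, so there is none to reproduce. The calculation below shows only what banding would cost.

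**Inputs from Statistical analysis.** 156 per group, 20% dropout, alpha 0.05 (taken as two-sided). Evaluable per arm: 156 × 0.80 = 124.8, taken as n = 125.

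**Assumptions, not in the article.** Normal scores; a treatment effect that shifts location by d standard deviations, with d = 0.3, 0.4 and 0.5; and the bands themselves, since no cut-points or number of categories are given.

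**Efficiency of banded against continuous scores**, for a small shift and an analysis that uses the order of the bands:

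e = Σ (φ(z_lower) − φ(z_upper))² / p, summed over bands, where φ is the normal density at the band limits and p is the band probability.

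- Median cut: φ(0) = 0.3989, so e = 2 × 0.3989² / 0.5 = 0.637.
- 16th-percentile cut: φ = 0.2433, so e = 0.2433² × (1/0.16 + 1/0.84) = 0.44.
- Quartiles: φ at the outer cuts = 0.3178, so e = 2 × 0.3178²/0.25 + 2 × (0.3989 − 0.3178)²/0.25 = 0.86.
- Deciles, same formula: 0.96.

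**Power** = Φ(d × √(n × e / 2) − 1.96). For d = 0.4:

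- continuous: 0.4 × √62.5 = 3.162, and Φ(1.202) = 88.5%
- median cut: 0.4 × √(62.5 × 0.637) = 2.523, and Φ(0.563) = 71%

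| Analysis | e | d = 0.3 | d = 0.4 | d = 0.5 |
|---|---|---|---|---|
| Continuous score | 1 | 66% | 88.5% | 98% |
| Deciles, ordered | 0.96 | 64% | 87% | 97% |
| Quartiles, ordered | 0.86 | 59.5% | 83.5% | 96% |
| Median cut | 0.64 | 47% | 71% | 88% |
| 16th-percentile cut | 0.44 | 35% | 56% | 75% |

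**Check on the single cuts.** A direct two-proportion calculation, with the second proportion equal to Φ(z − d), gives 47%, 70% and 87% for the median cut. For the 16th-percentile cut it gives 31%, 48% and 64%. The approximation is close at the median and somewhat generous at the low cut.

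**If the order of the bands is not used.** A chi-square test on k bands has k − 1 degrees of freedom and non-centrality n × e × d²/2. At d = 0.4:

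- quartiles: 125 × 0.861 × 0.16/2 = 8.61 on 3 df, power 69%
- deciles: 125 × 0.959 × 0.16/2 = 9.59 on 9 df, power 54%

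Many bands therefore protect power only if their order enters the analysis.

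**The case against.** The strongest reply is that the article never says that scores will be collapsed coarsely. Table 1 uses the same formula for the mRS, where each score can be its own category and nothing is lost. Percentile ranks could be read the same way. Band definitions are a detail that an article leaves to the full protocol or analysis plan, and ordered deciles would cost only 1 to 2 points of power. This stands as a limit on the size of the loss. It does not remove the point: the neuropsychological measure is stated as categories twice, and unassigned linear models elsewhere do not change it.

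For quality of life the reply is stronger. The text compares scores, and the EQ-5D-3L domains are three-level items, so counts by level lose nothing there. Only the EQ VAS and any total score could be affected.

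A reader might infer that both sets of scores are fixed as counts and that no outcome is left for a linear model. The documents do not support this: the outcomes text names quality-of-life scores as a comparison, and the statistical section supplies a model that could take them. A reader might also infer that a set share of the patients' information is thrown away. No such figure can be given, because the bands are not stated.

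Finally, the abstract describes these investigations as exploratory, and they carry no power target.

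**Conclusion.** The point holds in a limited form. For neuropsychological status, the article states a less efficient measure than the data allow. For quality of life, Table 1 and the outcomes text need to be reconciled.

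If the scores are banded, the loss of efficiency runs from about 4% (ordered deciles) to about 56% (one cut at the 16th percentile). A median cut would cost roughly 10 to 19 points of power over effects of 0.3 to 0.5 SD. These figures rest on normality, a pure location shift, 125 evaluable patients per arm and illustrative bands, none of which the article gives for these outcomes.

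The primary outcomes and the 156 per group are untouched. Severity is low to moderate, because the outcomes are secondary and exploratory.

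**What to change.** In Table 1 and the text after it:

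- Define the neuropsychological comparison as the between-group difference in mean norm-referenced score for each test, at 6 and 24 months.
- Define the comparison for the EQ VAS, and for any total quality-of-life score, as the difference in means at 3, 6, 12 and 24 months.
- Use the linear model already named for both, with robust or bootstrap standard errors.
- Keep the EQ-5D-3L domains as ordinal levels.
- Keep percentile bands as descriptive tables.

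The cost is wording; no new data, visits or patients are needed. There are two drawbacks. Some scores are skewed or have floor effects, which is why robust or bootstrap errors are proposed. Mean differences are also less directly readable than clinical bands, which the descriptive tables would offset. The choice of covariates is a separate matter and need not change here.
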